## Abstract

**Background:**

Many stroke survivors remain with residual cognitive and motor impairments despite receiving timely acute and sub-acute rehabilitation. This indicates that rehabilitation following stroke should be continuous to meet the needs of individual stroke patients. Both cognitive and motor functions are essential for mastering daily life and, therefore, should be aimed at with rehabilitation. Exergames, motor-cognitive exercises performed using video games, are an auspicious method to train both motor and cognitive functions and at the same time may foster the long-term motivation for training. This study aims to assess the effect of concept-guided, personalised, motor-cognitive exergame training on cognitive and motor functions in chronic stroke survivors.

**Methods:**

This study is a single-blinded, randomised controlled trial. Assessments are performed at baseline, after a 12-week intervention, and at a 24-weeks follow-up. Chronic stroke patients (≥ 18 years old, ≥ 6 months post-stroke) able to stand for 3 min, independently walk 10 m, follow a two-stage command, and without other neurological diseases apart from cognitive deficits or dementia are included. Participants in the intervention group perform the exergame training twice per week for 30 (beginning) up to 40 (end) minutes additionally to their usual care programme. Participants in the control group receive usual care without additional intervention(s). Global cognitive functioning (total Montreal Cognitive Assessment (MoCA) score) is the primary outcome. Secondary outcomes include health-related quality of life, specific cognitive functions, single- and dual-task mobility, and spatiotemporal gait parameters. The target sample size for this trial is 38 participants. Linear mixed models with the post-outcome scores as dependent variables and group and time as fixed effects will be performed for analysis.

**Discussion:**

Superior improvements in global cognitive functioning and in the abovementioned secondary outcomes in the intervention group compared to the control group are hypothesised. The results of this study may guide future design of long-term rehabilitation interventions after stroke.

**Trial registration:**

ClinicalTrials.gov (NCT05524727). Registered on September 1, 2022.

**Supplementary Information:**

The online version contains supplementary material available at 10.1186/s13063-024-08283-7.

## Administrative Information

Note: the numbers in curly brackets in this protocol refer to SPIRIT checklist item numbers. The order of the items has been modified to group similar items (see http://www.equator-network.org/reporting-guidelines/spirit-2013-statement-defining-standard-protocol-items-for-clinical-trials/).

## Introduction

### Background and rationale {6a}

Stroke is a dominant global health burden and a major cause of long-term disability in adults [1–4]. In Switzerland, approximately 20,000 persons suffer a stroke each year [5]. A stroke can cause motor and cognitive impairments [6, 7]. The most common motoric consequence of stroke is hemiparesis, a unilateral paralysis or weakness of either one or both extremities [8]. It occurs in up to 80% of patients with stroke [9]. Hemiparesis typically leads to gait and balance impairments [10, 11], which can restrict mobility and independent ambulation [12]. Common cognitive impairments after stroke include deficits in executive functions, attention, spatial perception, and psychomotor processing speed [13, 14]. These cognitive impairments occur in a comparable frequency as motor impairments; depending on the specific cognitive function, 30 to 90% of stroke survivors suffer from cognitive impairment [7, 15, 16].

Residual impairments, consequences from the stroke lasting after the acute and sub-acute rehabilitation phase, are common after stroke [17, 18]. This is especially true for cognitive impairments. It is striking in this context that cognitive impairments have so far gained much less attention in research compared with motor impairments notwithstanding the fact patients mentioning ‘What are the best ways to improve cognition after stroke?’ being one of their foremost research priorities in relation to life after stroke [19]. Remaining cognitive deficits are often responsible for limited independence and quality of life in patients, who have regained good motor functioning and activities-of-daily-living ability [20]. The optimal treatment of cognitive deficits in chronic stroke patients is a clearly identifiable research gap [17, 21].

Motor-cognitive training is a comprehensive rehabilitation method that combines motor and cognitive training [22]. Combined motor-cognitive trainings may be an auspicious method to tackle this research gap. Motor-cognitive trainings can either be performed sequentially (first motor training component, then cognitive training component, or vice versa) or simultaneously (both task components executed at the same time) [22, 23]. Simultaneous motor-cognitive trainings, where both tasks are executed concurrently, may have the highest relevance for daily life, because daily life almost exclusively sets combined challenges [22]. Motor and cognitive functions have been shown to share structural and functional roots [24]. Fittingly, the ‘guided plasticity facilitation’ model suggests that motor-cognitive training can lead to additional benefits due to interaction effects of the two components [25, 26]. Confirming the theory, multiple systematic reviews in healthy older adults found that combined motor-cognitive trainings were superior in improving motor, cognitive, and dual-task functions [27–35]. In (chronic) stroke, however, there is less and yet unclear evidence. While first systematic reviews report beneficial effects of motor-cognitive over single interventions on balance and gait [36, 37], the effects on cognitive functions remain unclear to date [37–39].

The most promising type of simultaneous motor-cognitive trainings may be exergames [37], cognitively demanding video games, which require the player to be physically active to complete the gaming tasks [40, 41]. Gamification of training and the use of virtual reality can increase the motivation for and adherence to exergame training [42–44], while also giving the training ecological validity [45]. In healthy older adults, exergames have been shown to improve motor and dual-task functions [46–51], while potential has been reported for improving cognitive functions [52–56]. In other neurological populations, exergames showed beneficial effects on balance, mobility, and walking capacity [57–62], while the evidence for improving cognitive functions with exergames is yet scarce and inconsistent [63–66]. In (chronic) stroke, exergames have been found a suitable adjunct to conventional rehabilitation for improving motor functions [67–69]. However, little is yet known about the effect of motor-cognitive exergames on cognitive functions in chronic stroke, so further studies are needed [37]. Moreover, in most previous studies including stroke survivors, motor-cognitive exergame interventions were applied without systematically considering training principles, especially personalised progression [37]. It is known, however, that applying training principles and personally tailoring the training to the individual is important for the success of any training intervention [70, 71]. Therefore, we developed a training concept considering the FITT-VP (frequency, intensity, time, type, volume, progression) training principles in combination with neuroplasticity and motor learning principles [70, 72]. Applying this concept, it is the aim of this study to investigate if adding motor-cognitive exergame training to usual care has a beneficial effect on the long-term rehabilitation of chronic stroke survivors and if global cognitive functioning and secondary outcomes can be improved compared to a control group who does not receive the exergame training.

### Objectives {7}

To address the gaps of knowledge regarding rehabilitation of cognitive functions and effects of motor-cognitive exergames in chronic stroke, the primary objective of this study is to evaluate the effect of a 12-week concept-guided, personalised, motor-cognitive exergame training when added to usual care, in comparison to the effect of usual care alone on global cognitive functioning in chronic stroke survivors.

The secondary objectives of this study are to explore (1) the acute and (2) the persistent effect up to a 12-week follow-up of the exergame intervention on health-related quality of life, specific cognitive functions (sub-functions of attentional, executive, and visuospatial functions), single- and dual-task mobility, and spatiotemporal parameters in chronic stroke patients.

### Trial design {8}

This study is a randomised, controlled trial (RCT) with two parallel arms, investigating the superiority of a concept-guided, personalised, motor-cognitive exergame training added to usual care over usual care alone. The trial employs a single-blinded approach, with outcome assessors being unaware of group assignments. The randomisation is performed with a 1:1 ratio using stratification by sex (female or male [73]) and cognitive impairment (MoCA ≥ 24 or MoCA < 24 [74]).

## Methods: participants, interventions, and outcomes

### Study setting {9}

This study takes place in different academic and rehabilitation hospitals in the Canton of Zurich, Switzerland.

### Eligibility criteria {10}

#### Inclusion criteria

Participants fulfilling all the following inclusion criteria are eligible for the study:Adults (≥ 18 years) with chronic stroke (≥ 6 months post-stroke, ischemic or haemorrhagic [75])Able to stand for 3 min and walk 10 m, Functional Ambulation Category (FAC) ≥ 3Able to follow a two-stage command (no MoCA threshold for inclusion was set to prevent exclusion of persons with subtle or specific cognitive deficits [76])Able to give informed consent as documented by signature

#### Exclusion criteria

Participants fulfilling one or more of the following exclusion criteria are not eligible for the study:Unable or not willing to give informed consentHaving been diagnosed with other neurological diseases (e.g. Parkinson’s Disease, multiple sclerosis), except cognitive deficits or dementiaClinical contra-indications for the study interventionUnable to follow the study intervention or the test for the primary endpoint (MoCA), e.g. due to a neglect, aphasia, or other language problemsOverlapping enrolment in another clinical trial

### Who will take informed consent? {26a}

Movement scientists and therapists who are part of the study team and have been trained for this task obtain written informed consent from participants, after they have been written and orally informed about the study, its benefits and risks, and their rights and had at least 24 h for consideration.

### Additional consent provision for collection and use of participant data and biological specimens {26b}

The consent includes collection and use of individually identifiable participant data for the study procedures (through members of the study team only) and for audit trials by the cantonal ethical committee and other local authorities. Moreover, participants consent that their de-identified data is used for the analysis and publication of the study results. This study does not involve collecting biological specimens for storage.

## Interventions

### Explanation for choice of comparators {6b}

Participants in the control group continue with their usual care and receive no additional intervention. They are called once a week to align for contact to the study team and to gather their physical and cognitive activity data (see the ‘ Intervention and further activity outcomes’ section). This comparator was chosen as the aim of this study is to determine the effect of additional motor-cognitive exergame training. This aim was based on systematic reviews, which recommend the application of exergame training in addition to usual care, aiming at increasing the amount of rehabilitation offered to patients [63, 67, 77].

### Intervention description {11a}

The intervention group receives concept-guided, personalised, motor-cognitive exergame training additionally to usual care. The personalised motor-cognitive exergame training for stroke (PEMOCS) concept, which guides the intervention, was developed specifically for this study and, in accordance with the Modified Consensus on Exercise Reporting Template (CERT) for Therapeutic Exercise Interventions [78, 79], published elsewhere [80]. It determines the training dosage with regards to frequency, intensity, time, type, and volume of the exercises, which are based on recommendations from scientific literature for motor-cognitive and exergame trainings in chronic stroke and healthy older adults. Participants train twice a week for 12 weeks (intervention period, see Fig. 1). Training sessions last between 30 (beginning) and 40 (end) minutes, progressing in duration for 2 min every second week and resulting in 840 min total planned training time (see Table 1). Additionally, the PEMOCS concept is designed to provide personalised progression and variability in training considering principles for neuroplasticity, motor learning, and training [80–83]. It was developed based on Gentile’s Taxonomy for motor learning [84] and tested for its feasibility in the target population [85]. In short, motor and cognitive tasks of the exergame training are allocated to various difficulty levels along a skill-progression scheme with three dimensions. Based on the participants’ subjective ratings of their perceived motor-cognitive task difficulty and their perceived performance (see ‘Intervention outcomes’), progression through the difficulty levels is determined individually for each participant. Therefore, the training is personalised within a standardised progression scheme. Additionally, variability rules ensure variation in training tasks.

**Fig. 1 Fig1:**
[figure not shown]
Study flow. Overview of the study procedures. ADH, adherence; CPL, compliance; PCA, physical and cognitive activities; (S)AE, (serious) adverse event; UC, usual care

**Table 1 Tab1:** Training variables of the intervention, describing the frequency, time, volume per week, and total volume of the concept-guided, personalised, motor-cognitive exergame training

**Time point**	**Frequency** [per week]		**Time** [min/session]		**Volume/week** [min]	**Total volume** [min]
Weeks 1–2	2	x	30	=	60	
Weeks 3–4	2	x	32	=	64	
Weeks 5–6	2	x	34	=	68	
Weeks 7–8	2	x	36	=	72	
Weeks 9–10	2	x	38	=	76	
Weeks 11–12	2	x	40	=	80	**840**

The training is performed using the exergame device Dividat Senso (Dividat AG, Schindellegi, Switzerland, for a detailed description of the device see [85]). The Dividat Senso consists of a TV screen and a pressure-sensitive plate as well as a handrail on three sides to provide security to trainees (Fig. 2). Participants perform stepping movements on the plate to control the games. The system provides real-time feedback on the gamer’s performance, including visual, auditory, and tactile cues facilitating the interaction of the participant with the video games. These video games target different cognitive functions (incl. attentional, executive, memory, and visuospatial functions). Via an online platform, personalised training programmes can be created within the Dividat training system.

**Fig. 2 Fig2:**
[figure not shown]
Study device: Dividat Senso in action. Pressure-sensitive plate with handrails on three sides and screen on head-height of the participant, showing the video game. The participant performs a stepping movement to play the game

### Criteria for discontinuing or modifying allocated interventions {11b}

The intervention is discontinued in case of withdrawal of the informed consent, participant request, or if the health status of the participant or any harm does not allow the continuation of the intervention. Minor individual modifications of the planned intervention are possible (e.g. using a training aid for additional stability) if following the training concept is possible.

### Strategies to improve adherence to interventions {11c}

All sessions are supervised one-to-one by a trained movement scientist, who engages the participant in the study procedures and encourages complying with the set appointments. Additionally, considering each individual’s game preferences is part of the PEMOCS concept’s variability rules to foster motivation and fun during the gaming sessions. Compliance with training sessions and adherence to scheduled training time are recorded.

### Relevant concomitant care permitted or prohibited during the trial {11d}

Concomitant care (usual care) including other therapies is allowed and recorded in both groups during the whole study.

### Provisions for post-trial care {30}

N/A, as there are no disadvantages likely to arise from the intervention.

## Outcomes {12}

Primary and secondary outcomes are collected at three time points (T0–week 0, T1–week 12, T2–week 24; see Table 2, Figs. 1 and 3) by cognitive and motor assessments as well as a health-related-quality-of-life questionnaire. At the baseline measurement (T0), participant characteristics and baseline factors are recorded. Intervention and activity outcomes are collected during the intervention (T0–T1) and the follow-up (T1–T2) periods, respectively. All variables will be aggregated as means or medians, depending on the distribution of the data, and the analysis metric for all will be final values (see the ‘ Statistical methods’ section). An overview of all outcome variables is presented in Tables 3 and 4.

**Table 2 Tab2:** Overview over outcome recording. *ADH*, adherence; *BBS*, Berg Balance Scale; *BQ*, baseline questionnaire, incl. see the ‘ Baseline factors’ section; *TUG(-Cogn)*, (cognitive dual-task) Timed Up and Go test; *CPL*, compliance; *FAC*, Functional Ambulation Category; *FM-LE*, lower-extremity component of Fugl-Meyer assessment; *MoCA*, Montreal Cognitive Assessment; *mRS*, modified Rankin scale; *MRT*, mental rotation test; *NBT*, N-back test; *NIHSS*, National Institute of Health Stroke Scale; *OWA*, outdoor walking assessment; *PCA*, physical and cognitive activities; *PP*, perceived performance; *PTD*, perceived task difficulty; *SIS 3.0*, Stroke Impact Scale; *SRT*, simple reaction test; *Stroop*, Stroop Interference test; *TMT*, Trail Making test; *UC*, usual care; *10MWT*, 10-m walk test

Time (weeks)	0	+ 1–12	+ 12	+ 13–24	+ 24
**Time point**	Baseline (T0)	Intervention period	Post-intervention (T1)	Follow-up period	Follow-up (T2)
**Study staff**	Assessor	Training supervisor	Blinded assessor	Training supervisor	Blinded assessor
**Baseline factors:** BQ, NIHSS, FAC, mRS, BBS, FM-LE	+				
**1° Endpoint:** MoCA	+		+		+
**2° Endpoints:** SIS 3.0, SRT, TMT, Stroop, NBT, MRT, TUG(-Cogn), 10MWT, OWA	+		+		+
**Intervention Endpoints:** CPL, ADH, PTD, PP		+ *(intervention group only)*			
**Activity Endpoints:** UC, PCA		+		+

**Fig. 3 Fig3:**
[figure not shown]
SPIRIT figure. ADH, adherence; BBS, Berg Balance Scale; BQ, baseline questionnaire, incl. see the ‘ Baseline factors’ section; TUG(-Cogn), (cognitive dual-task) Timed Up and Go test; CPL, compliance; FAC, Functional Ambulation Category; FM-LE, lower-extremity component of Fugl-Meyer assessment; MoCA, Montreal Cognitive Assessment; mRS, modified Rankin scale; MRT, mental rotation test; NBT, N-back test; NIHSS, National Institute of Health Stroke Scale; OWA, outdoor walking assessment; PCA, physical and cognitive activities; PP, perceived performance; PTD, perceived task difficulty; SIS 3.0, Stroke Impact Scale; SRT, simple reaction test; Stroop, Stroop Interference test; TMT, Trial Making test; UC, usual care; 10MWT, 10-m walk test

**Table 3 Tab3:** Overview of primary and secondary outcomes with definitions. *TUG-Cogn* cognitive dual-task Timed Up and Go test, *MoCA* Montreal Cognitive Assessment, *MRT* mental rotation test, *NBT* N-back test, *OWA* outdoor walking assessment, *SIS 3.0* Stroke Impact Scale, *SRT* simple reaction test, *TMT* Trail Making test, *TUG* Timed Up and Go test, *10MWT* 10-m walk test. *The asymmetry index is calculated according to the presented formula not considering affected body side. Allocating left and right in the formula has an impact on the algebraic sign of the asymmetry index, not, however, on its absolute value. As absolute values will be reported for comparability of the asymmetry indices of left- and right-affected patients, the formula can be used as reported [86]. ** [87]

Test	Outcome variables	Definition
**Primary outcome**		
MoCA	Total score (0–30)	= Sum of domain scores + 1 point for participants with ≤ 12 years of education and a MoCA score < 30
**Secondary outcomes**		
SIS 3.0	- Total score (0––100)	= Sum of domain scores
	- Perceived recovery (0–100%)	Collected by visual analogue scale
	- Domain scores (0–100%): strength, memory/thinking, emotion, communication, ADL/IADL, mobility, hand function, participation	$$=\frac{\text{Sum of Likert ratings}}{\textrm{Number of items}}\times 100$$
SRT	Of all six conditions:	
	- Reaction time	= Logarithmic mean of trial reaction times
	- Missed	Number of non-answered stimuli within 1500 ms
	- Mistakes	Number of reactions upon no stimulus
TMT A&B	- Time A, time B	Processing time of each sub-test
	- Mistakes A, mistakes B	Number of incorrect touches in each sub-test
	- B to A ratio	$$=\frac{\text{Time B}}{\textrm{ Time A}}$$
Stroop	For reading and naming:	
	- Interference tendency	= Median RT interference – median RT baseline
	Of all four conditions:	
	- Reaction time	= Median reaction time of all trials
	- Mistakes	Number of false reactions
NBT	- Correct	Number of correct responses (stimulus inquired a reaction and participant responded)
	- Omissions	Number of missed responses (stimulus inquired a reaction but participant did not respond)
	- Mistakes	Number of incorrect responses (stimulus inquired no reaction but participant responded)
	- Reaction time (correct)	= Mean reaction time of correct responses
	- Reaction time (mistakes)	= Mean reaction time of incorrect responses
MRT	- Accuracy	$$=\frac{\text{Number of correct responses}}{\textrm{ Total number of tasks}}$$
	- Reaction time	= Mean reaction time of correct responses
TUG	- Time TUG	= Mean time of the 3 motor single-task trials
	- Type of cognitive task	Serial subtraction or verbal fluency
	- Correct response rate single-task (CRR_single_)	= Mean CRR of the 3 cognitive single-task trials
		CRR $$=\frac{\text{Number of correct responses}}{\text{ Time}}$$
	- Time TUG-Cogn	= Mean time of the 3 dual-task trials
	- Correct response rate TUG-Cogn (CRR_dual_)	= Mean CRR of the 3 dual-task trials
	- Motor dual-task effect (DTE%_motor_)	$$=\frac{\text{Time TUG-Cogn - Time TUG}}{\textrm{Time TUG}}\times 100$$
	- Cognitive dual-task effect (DTE%_cognitive_)	$$=\frac{{\text{CRRdual-CRRsingle}}}{{\textrm{CRRsingle}}}\times 100$$
10MWT,	- Time	= Mean time for 10m of the three trials
preferred	- Gait speed (preferred)	= Mean gait speed
		Instruction: ‘Walk at a comfortable speed’
	- Cadence	= Mean steps/min
	- Stride length	= Mean stride length
	- Stride length variability	= Mean stride length variability
	- Stride time	= Mean stride time
	- Stride time variability	= Mean stride time variability
	- Double support time	= Mean double support time
	- Stance phase affected, unaffected	= Mean stance phase
	- Swing phase affected, unaffected	= Mean swing phase
	- Swing width affected, unaffected	= Mean swing width
	- Asymmetry index*	$$=\frac{\text{Swing phaseleft - Swing phaseright}}{\textrm{ 0.5 (Swing phaseleft + Swing phaseright)}} \times 100$$
	- Walk ratio**	$$=\frac{\text{Mean Corrected Stride Length/2}}{\textrm{ Corrected Cadence}}$$
10MWT,	- Time (fast)	= Mean time for 10m of the three trials
fast		Instruction: ‘Walk as fast but safe as possible’
OWA	- Gait speed (preferred)	= Mean gait speed
		Instruction: ‘Walk at a comfortable speed’
	- Cadence	= Mean steps/min
	- Stride length	= Mean stride length
	- Stride length variability	= Mean stride length variability
	- Stride time	= Mean stride time
	- Stride time variability	= Mean stride time variability
	- Double support time	= Mean double support time
	- Stance phase affected, unaffected	= Mean stance phase
	- Swing phase affected, unaffected	= Mean swing phase
	- Swing width affected, unaffected	= Mean swing width
	- Asymmetry index*	s. above
	- Walk ratio**	s. above

**Table 4 Tab4:** Overview of intervention and further activity outcomes. *CA* cognitive activities, *CT* cognitive therapy, *PA* physical activities, *PT* physical therapy

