### Secondary outcomes

Health-related quality of life and perceived recovery are assessed using the total score and the single domain scores of the Stroke Impact Scale [SIS 3.0 [103]]. The SIS 3.0 is a stroke-specific questionnaire assessing the self-reported health status on 5-point Likert scales [98]. It encompasses eight domains (strength, memory/thinking, emotion, communication, ADL/IADL, mobility, hand function, and participation) and a visual analogue scale, where the perceived state of recovery is rated (0 to 100%) [98]. The final score lies between 0 and 100, where a higher score indicates better health-related quality of life. The German SIS (DE-SIS, translated and cross-culturally adapted) was found reliable and valid for the use in German-speaking stroke survivors [104].

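### The SIS 3.0 scoring formulas in Table 3 cannot produce the 0–100 ranges printed beside them, for either the domain scores or the total

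*Protocol article*

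**What the plan says.** Table 3 of the protocol article lists the SIS 3.0 variables with a range and a definition for each.

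- **Domains.** The row reads "Domain scores (0–100%): strength, memory/thinking, emotion, communication, ADL/IADL, mobility, hand function, participation". The definition is a fraction with "Sum of Likert ratings" over the number of items, multiplied by 100.
- **Total.** The row gives the range as "Total score (0––100", and the definition is "Sum of domain scores".

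The text under 'Secondary outcomes' describes the questionnaire as "assessing the self-reported health status on 5-point Likert scales" and says of its content: "It encompasses eight domains". It repeats the range of the total: "The final score lies between 0 and 100, where a higher score indicates better health-related quality of life".

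The article does not print the numeric codes of the five response options. It also gives no step that subtracts a minimum, divides by the width of the response scale, or averages over domains.

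**The concern.** Dividing a sum of ratings by the number of items gives the mean rating. Multiplying that by 100 gives a percentage only if a rating runs from 0 to 1, and a 5-point rating does not. The total has a separate problem: eight scores that can each reach 100 cannot have a sum capped at 100.

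Health-related quality of life is named in the secondary objectives, and SIS is the instrument that measures it. The 'Outcomes' section makes final values the analysis metric, so reported SIS means and group differences carry whatever scale the scoring rule sets. 'Methods for additional analysis' also compares group differences and individual change with clinically meaningful change scores. An inflated scale would make a given change look larger against such a threshold.

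**Working it through.** **Inputs**

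- Domain formula, total formula and both stated ranges: Table 3.
- Five response options and eight domains: text under 'Secondary outcomes'.
- Numeric codes of the options: not given. I take 1–5 as the ordinary reading and also try 0–4 and items already rescaled to 0–1.

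**Step 1. Domain score as printed.** For k items, the score is (sum of ratings / k) × 100 = mean rating × 100, whatever k is.

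| Item coding | Lowest | Highest | Stated range |
|---|---|---|---|
| 1–5 | 1 × 100 = 100 | 5 × 100 = 500 | 0–100% |
| 0–4 | 0 × 100 = 0 | 4 × 100 = 400 | 0–100% |
| 0–1 (rescaling not stated) | 0 | 1 × 100 = 100 | 0–100% |

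Only the third row reproduces the stated range, and it needs a rescaling of the items that the article does not mention.

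**Step 2. Total as printed.** Give every domain exactly its stated range of 0–100. The sum of eight then runs from 8 × 0 = 0 to 8 × 100 = 800. The stated range is 0–100. This step does not depend on item coding, so no coding satisfies both rows of the table.

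**Step 3. Size of the error in a domain.** Under the printed formula, one point on the mean rating is worth 100. On a 0–100 scale built from five options it is worth 100/4 = 25. The ratio is 100/25 = 4, under either 1–5 or 0–4 coding. A change of 3 points on the 0–100 scale would be recorded as 3 × 4 = 12.

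**Step 4. A correction that works.** For 1–5 coding, ((mean rating − 1)/4) × 100 gives (1 − 1)/4 × 100 = 0 at the bottom and (5 − 1)/4 × 100 = 100 at the top. Dividing by the maximum possible sum alone is not enough: 1/5 × 100 = 20 and 5/5 × 100 = 100, a range of 20–100. With domains corrected, their sum still runs 0–800, while their mean runs 0–100.

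**Step 5. What does not change.** If all items share one coding and direction, the printed domain score is a linear transform of a 0–100 score. With all eight domains present, the sum differs from the mean only by the constant factor 8. A linear mixed model returns the same test statistics and p-values under such a transform. The planned effect size r, a correlation coefficient, is unchanged too.

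**The case against.** The intended scale is clear. The 0–100 bound is printed for the domains, for the total, and again in the text, and the article cites the instrument and its validated German version. A value of 350 on a scale labelled 0–100% would be noticed at once, and 'Data management' has a second investigator check the entry of secondary outcomes. The formulas may be shorthand in a summary table, and nothing in the article shows that the eCRF or the code uses them.

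Much of this stands, and it limits the consequence. It does not remove the contradiction. Table 3 is presented as giving definitions, and its neighbouring formulas, such as the dual-task effects and the asymmetry index, are meant to be applied as written. The second check is a check of data entry; it is not described as a check of the scoring rule.

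Three stronger readings are tempting, and the documents do not support them.

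- **That reported SIS results will be wrong.** This follows only if the formulas are applied literally. Even then, raw-unit means and differences are affected, while p-values and r are not.
- **That responder counts will be wrong.** 'Methods for additional analysis' runs that step only for outcomes with a significant group effect at T1 or T2 and a clinically important difference in the literature. Its one worked example is 1.22 points on the MoCA. The article gives no SIS threshold.
- **That the total runs 800–4000, or is inflated 32-fold.** The first figure needs 1–5 coding (8 × 100 and 8 × 500). The second (4 × 8) assumes that the correct total is the unweighted mean of eight domains. The article states neither.

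**Conclusion.** The point holds as an internal contradiction in a stated scoring rule. The total row conflicts with its own range and with the text under any item coding: 0–800 against 0–100. The domain row conflicts with its range under both ordinary codings: 100–500 for 1–5, or 0–400 for 0–4, against 0–100%.

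If the printed formulas were used, domain means and differences would be off scale, with differences inflated 4-fold. A comparison with a published threshold could be wrong if SIS became significant and a threshold existed. The invariance of p-values and r rests on one coding and direction for all items and, for the total, on complete domains. The MoCA analysis and the sample size are untouched. The point deserves correction because the scale of a reported secondary outcome depends on it, but it does not threaten the trial's main conclusion.

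**What to change.** In Table 3:

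1. State the numeric coding of the five response options.
2. Replace the domain formula with (mean rating − minimum)/(maximum − minimum) × 100, which is ((mean rating − 1)/4) × 100 if items are coded 1–5.
3. Replace the summed total with a rule that yields 0–100, taken from the cited instrument's scoring instructions. The mean of the eight domain scores is one rule that would do so; the article alone does not settle which rule the instrument prescribes.

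Then confirm that the eCRF and the analysis code use the corrected formulas, and that any SIS threshold used later is on the same scale. The cost is two table cells, one line on coding and a code check. No new data are needed, because the scores can be recomputed from the item ratings.
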